### Intervention

Two different programs are designed in order to investigate the effect of PA on mitochondrial function in skin fibroblasts of patients with PD.

The first group (n = 8) will undergo basic physical training (BPT) focused on strength and resistance. The second group will engage in BPT combined with functional exercises (BPTFE), which includes cognitive and dual task training. A third group, the sedentary group, will serve as the control. The intervention in the two PA programs will last 3 months.

The interventions will be conducted in group settings, with 8 patients per group, and each session will last for 60 minutes. The frequency of the sessions will be 3 times a week. The intervention programs will be structured into 3 meso-cycles of 4 weeks. During the initial two weeks, the workloads will be maintained to facilitate the adaptation period. For the BPTFE program, in addition to adapting to the load, participants will also need to adapt to complex motor execution tasks. Starting from the third week, the workload will progressively increase.

In both PA programs, exercises will target the large muscle groups, with a component/emphasis on the eccentric phase of concentration. The *kBox4* Platform, a device designed to maximize performance and training outcomes, will be used to enhance the eccentric phase of the exercises. This device, provided by Exxentric AB (Stockholm, Sweden), a company specialized in innovative and evidence-based training equipment and methods, will be loaned for the study. *kBox4* is controlled by a specific program, *Kmeter*, which records and stores all the information (duration, intensity, repetitions, etc.) of each movement. Exxentric *kBox4* will be adapted with special harnesses, insurances on the wall and in front of support bars, according to the needs of the patients. In addition to the major muscle groups, specific attention will be given to the key muscles involved in the gait cycle, such as the tibialis anterior, medial gastrocnemius, rectus femoris, and hamstrings, from a biomechanical perspective. This aspect will be common to both programs, with the only difference being that the BPT program will have a greater workload due to the division of activity time between functional exercises and Dual Task Training in the BPTFE program.

### Experimental groups

#### Intervention group 1—Basic Physical Training (BPT)

This PA program will be based only on the work of BPT, in
which
specifically
and
mainly
the
Strength (S) and
Resistance (R) will
be worked, but
also
flexibility.

#### Intervention group 2—Basic Physical Training with Functional Exercises (BPTFE)

In addition to the BPT program (which includes the transverse focus on strength and resistance exercises), this intervention group will incorporate functional exercises that involve dual task training. The dual task training can encompass both motor-motor and motor-cognitive activities. This means that coordinated exercises will be performed, with cognitive activities introduced at the extremes of the movement. This approach ensures engagement of both physical and cognitive abilities during the PA sessions.

### Control group—Sedentary (Sed)

Participants in the control group will maintain their regular daily routines throughout the study period. Weekly interviews will be conducted by the researchers to ensure that their routines remain unchanged and to minimize any effect due to the interaction with the researchers. After the final evaluation, at the end of the study (6 months), this group will receive 3 months of PA based on the program that has obtained the most favorable outcomes, in terms of symptoms management and quality of life.

### Outcome assessment and measurement procedures

The primary outcome of the PARKEX study is the mitochondrial (dys)function, while secondary outcomes include motor
function, quality
of
life, sleep, cognitive aspects and
mood. Additionally, the study aims to perform the metabolic characterization of cutaneous fibroblasts from PD patients, evaluating the
effects
of PA-induced metabolic remodeling on oxidative stress, mitochondrial quality control, mitochondrial DNA copy number, mitochondrial protein expression and transcript levels in skin fibroblasts of PD patients.

To gather pre-intervention
and
post-intervention
clinical parameters, the following experimental
design procedures will be followed in 2 different phases (see Tables 1 and 2 and Fig 3).

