### Sample size calculation

The sample size for this study was determined using the GRANMO program with the model of observed proportions with respect to a reference. For the calculation it has been taken into account that the "maximal respiration” is the key indicator to determine the effects of PA on mitochondrial function, because the entire respiratory chain is forced to the maximum. The calculation has been made accepting an **α** risk of 0.05 and a beta risk of less than 0.2 in a two-sided contrast. Based on preliminary data, there is a difference of "maximal respiration" equal to or greater than 0.263 units [23]. It is assumed that the proportion in the reference group is 0.019 in people older than 50 years [30]. Being an interventional study, the percentage of necessary replacements has been predicted to be 20%.

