Evaluate the effect of PA on mitochondrial remodeling in skin fibroblasts from patients with PD, namely in the mitochondrial maximal respiration	Assess the effects of metabolic remodeling on mitochondrial oxygen consumption rate, oxidative stress, mitochondrial quality control, mitochondrial DNA copy number, mitochondrial proteins and transcripts	Characterize the effects of PA remodeling on fibroblast from patients with PD, in terms of mitochondrial biogenesis, oxidative stress, and mitochondrial quality control	- Determination of oxygen consumption rate (OCR) and extracellular acidification rate (ECAR) using a Seahorse XFe96 Extracellular Flux Analyzer (Agilent Technologies, Germany). - qRT-PCR (using SsoFast Eva Green Supermix, in a CFX96 real time-PCR system (Bio-Rad, Hercules, CA, USA)) for transcripts of interest related to mitochondrial biogenesis, dynamics, epigenetic regulation, oxidative phosphorylation, oxidative stress (SOD1, SOD2, NFE2L2), quality control mechanisms, including autophagy and ubiquitin-proteasome system (UPS). - Regulation and abundance of mitochondrial proteins by immunoblotting Enzymatic activities (ex, mitochondrial complex I and citrate synthase)

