### Mitochondrial analysis

The analysis of mitochondrial function and metabolism in skin fibroblasts from patients will encompass various parameters. Metabolic fluxes of the cells will be assessed using the Seahorse XF^e^96 Extracellular Flux Analyzer [23]. Additionally, mitochondrial membrane potential and morphology will be evaluated using TMRM staining, while cellular oxidative stress will be measured using hydroethidine (HEt) and CM-H2DCFDA. Moreover, ATP levels will be determined using a high-throughput luminescent method [37]. The expression of relevant transcripts associated with mitochondrial biogenesis, stress responses, oxidative phosphorylation, and auto(mito)phagy will also be evaluated [23]. This includes enzymes such as superoxide dismutase, catalase [38], glutathione reductase, parkin and PINK1 proteins, the mitochondrial transcription factor A (TFAM), the regulator of mitochondrial biogenesis (such as PGC1-α), and metabolism (such as AMPK-α) [37]. The evaluation of these parameters aims to unravel the molecular mechanism through which PA promotes mitochondrial metabolism remodeling in PD patients. Furthermore, this analysis seeks to identify new intervention targets for PD and demonstrate, for the first time, that the metabolic and mitochondrial beneficial effects of PA in PD patients can be detected through observable biochemical changes in their skin fibroblasts. By uncovering these biochemically-detectable alterations, we can gain valuable insights into the specific mechanisms underlying the metabolic and mitochondrial improvements resulting from PA, providing a foundation for targeted interventions in PD.

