### Statistical analysis

Data
analysis
will
be performed using SPSS v.20 (IBM SPSS Statistics). Regarding
descriptive
analysis, all
the variables of
the
sample
will
be analyzed by
means
of
relative
and
absolute frequencies, as
well
as measures of dispersion and
central
tendency frequencies. Repeated measures analysis will be performed using the appropriate mixed effects model, accounting for homogeneous or inhomogeneous samples. This analysis will determine the possible changes between the different moments of the intervention and to evaluate which types of intervention yield the greatest physical benefits, whether in terms of mitochondrial function, physiological factors, quality of life, or cognitive and emotional aspects. Spearman’s
rho
and Pearson’s
r
will
be
used
to
evaluate
the
association
between
two variables that
have
ordinal categories. The
normality
of
the
distribution
of
the results for each
group´s results will
be assessed using the Shapiro-Wilk normality
test, with a significant threshold set at α = 0.05. If
the
data follow a normal
distribution, a parametric paired t-test will be conducted. Otherwise, the Mann-Whitney test
will
be
used. Statistical significant differences will be considered for statistical test
values
with
p<0.05.

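### The primary outcome is a whole domain in one section but maximal respiration in two others, with a flat p<0.05 and no primary contrast among three arms

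*Protocol article*

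**What the plan says.** Four parts of the protocol article bear on this.

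- **Outcome assessment and measurement procedures:** "The primary outcome of the PARKEX study is the mitochondrial (dys)function". The sentence gives no variable, time point or contrast. A following sentence, opening with the word additionally, lists oxidative stress, quality control, mitochondrial DNA copy number, proteins and transcripts as further aims.
- **Sample size calculation:** maximal respiration "is the key indicator to determine the effects of PA on mitochondrial function", and it is the only measure used to size the trial.
- **Table 2:** the cell under the primary-measures column speaks of mitochondrial remodeling, "namely in the mitochondrial maximal respiration". The other cells of the same entry hold the wider battery. The objectives cover "oxygen consumption rate, oxidative stress, mitochondrial quality control, mitochondrial DNA copy number, mitochondrial proteins and transcripts", and the analysis column adds OCR and ECAR, a range of transcripts, immunoblotted proteins and enzyme activities. The Mitochondrial analysis section adds more, for example "mitochondrial membrane potential and morphology will be evaluated using TMRM staining". Table 1, which lists the secondary outcomes, contains none of these.
- **Statistical analysis:** "Statistical significant differences will be considered for statistical test" values below 0.05. The section plans a mixed effects model to find which intervention does best, and refers to mitochondrial function again as a domain. It names no primary comparison among the three arms.

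**The concern.** Which variable is primary is for the protocol to settle. Here one section names a domain, and two others name one variable within it. Most of the remaining assays are set apart in the text of the outcome section, yet they appear in the table of primary measures and are missing from the table of secondary ones, so their standing is open.

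This matters because the analysis section has one threshold for everything and three arms to compare. Suppose maximal respiration shows nothing but a transcript or an enzyme activity differs between two arms at p<0.05. A report could then say that exercise changed mitochondrial function, and the outcome section's wording would support it. The Mitochondrial analysis section hopes to show for the first time that exercise benefits can be detected in patients' fibroblasts. A claim of that kind needs a main test whose error rate is known.

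**Working it through.** **1. What the trial was sized for.** Inputs from the sample size section: reference proportion 0.019; difference 0.263, so the alternative is 0.019 + 0.263 = 0.282; an alpha "risk of 0.05 and a beta risk of less than 0.2 in a two-sided contrast", so z = 1.960 and 0.8416; 20% replacements. The stated model is one observed proportion against a reference:

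n = [1.960·√(0.019·0.981) + 0.8416·√(0.282·0.718)]² / 0.263² = (0.2676 + 0.3787)² / 0.0692 = 6.04

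6.04 / 0.80 = 7.55, rounded up to 8 per arm, and 3 × 8 = 24. The stated size reproduces. (Rounding 6.04 up to 7 first gives 7 / 0.80 = 8.75, or 9 per arm.) The calculation covers one variable and one comparison at 0.05. It makes no allowance for several readouts or several pairs of arms. Whether a one-sample proportion model suits this outcome is a separate question.

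**2. Maximal respiration alone.** Null simulation: 20,000 runs, three arms of 8, normal change scores, each test at 0.05.

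- One three-arm (2-df) test: about 5%.
- Success if either exercise arm differs from control: about 9%.
- Success if any of the three pairs differs: about 12%. Three independent tests would give 1 − 0.95³ = 14.3%. The simulated figure is lower because the pairs share arms.

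**3. If every readout counted as primary.** The article gives no count of readouts, so 4, 6 and 10 are assumptions. So is the common correlation between readouts, varied from 0.8 to 0. Chance of at least one p<0.05 when nothing differs:

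| Readouts (assumed) | One three-arm test each | All three pairs each |
|---|---|---|
| 4 | 13-18% | 27-41% |
| 6 | 15-27% | 31-54% |
| 10 | 19-40% | 38-73% |

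The low end of each range is correlation 0.8 and the high end is correlation 0. As a check on the middle column, independence gives 1 − 0.95⁴ = 18.5%, 1 − 0.95⁶ = 26.5% and 1 − 0.95¹⁰ = 40.1%, in line with its high ends.

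**4. What the two sources of error contribute.** Settling on one variable removes the growth down the rows of the table. It does not remove the 12% from the three pairs, which needs a named contrast, a gate or an adjustment.

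**5. Whether a gate suffices.** With three arms, any two pairwise null hypotheses together imply that all three arms are equal. The 2-df test addresses exactly that hypothesis. If it is significant at 0.05, each pair can be tested at 0.05 without inflating the overall error; this is a closed test. Bonferroni over three pairs would instead require 0.05 / 3 = 0.0167 each.

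**The case against.** The best defence is that the article does identify its primary variable. In Table 2 the primary measures are a column, not a row, and the cell in that column narrows to maximal respiration. The battery stands under the columns for objectives, description and analysis methods. The outcome section introduces most of the other readouts as additional, and the sample size rests on maximal respiration alone. The p<0.05 statement is a general threshold and does not make each assay a criterion of success. Multiplicity procedures are also commonly left to a statistical analysis plan, and neither that plan nor the full protocol is shown.

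Most of this stands. A reader might infer that the assays are co-primary and that a chance primary success is more likely than not. The documents do not support that. No section declares the assays co-primary or prescribes all pairwise tests. The error passes one half only with many weakly correlated readouts, all three pairs tested and every readout counted. Multiplying readouts by pairs and treating all the tests as independent would overstate it further, because the pairs share arms. Nor is the lack of an adjustment method in a condensed article a fault in itself.

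What the defence does not remove is the mismatch in the definition. The sentence that formally states the primary outcome is broader than the variable given elsewhere, and the analysis section repeats the broad term.

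**Conclusion.** The point holds as an inconsistency in how the primary outcome is defined, together with an unprotected comparison of three arms. The text allows a primary claim to rest on maximal respiration, on another assay, or on whichever pair of arms differs.

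Read narrowly, with maximal respiration alone, the false-positive rate runs from about 5% (one three-arm test) to about 12% (any of three pairs). Read broadly, with 4 to 10 readouts, it is about 13-40% with three-arm tests and about 27-73% with all pairs. These figures assume 8 analysed patients per arm, normally distributed changes, a common correlation between 0 and 0.8, and no adjustment elsewhere. The broad figures show what the loose wording would permit; they are not a forecast of what the investigators will do. An analysis plan that is not shown may already settle the order of tests, but the article's own definition would still need to agree with it.

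**What to change.** - **Outcome section:** state that the single primary outcome is fibroblast maximal respiration at the post-intervention biopsy (3 months), in agreement with the sample size section and the primary-measures column of Table 2.
- **Statistical analysis:** test that outcome first with one 2-df comparison of the three arms at 0.05. In the planned mixed model with measurements before and after the intervention, this is the arm-by-time test. Test the pairs at 0.05 only if it is significant.
- **Table 2 and Mitochondrial analysis:** label all other assays secondary or exploratory, with no claim on the primary objective.

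The change is to wording only; no visit, biopsy or assay is affected. The trial status section places analysis after the last follow-up, so at the time of the article the definition could still be fixed before results were seen. The cost is that an isolated significant assay can no longer be called a primary finding, and that a single significant pair does not count when the three-arm test is not significant.

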**Fig 3 pone.0293774.g003:**
[figure not shown]
Graphical representation of PARKEX study design. Study design highlighting the interventions and respective experimental groups, timing of sample collection, and analyzed.

**Table 1 pone.0293774.t001:** Phase 1 in Spain. Secondary outcome measures and their assessment instruments.

Secondary outcome measures	Instruments to assess the study variable
**Functional Assessment—Balance**	TINETTI scale and BERG Balance Scale
**Functional Assessment**	Six-minute walk test (6MWT)
	1-minute sit-to-stand test (STS). Times you get up and sit down, in a chair
	Timed Up and Go (TUG). Time to get up from a chair, walk 3 m, turn around, walk backwards and sit down
**Motor function**	Movement Disorder Society—Unified Parkinson’s Disease Rating Scale (MDS-UPDRS I-III)
**Cognitive aspects**	Montreal Cognitive Assessment (MoCA)
**Quality of life**	Parkinson’s Disease Questionnaire (PDQ-39)
**Humor (Profile of Mood States)**	BDI-2 Beck’s Depression Inventory
**Sleep quality**	Parkinson’s Disease Sleep Scale–2 (PDSS‐2)
**Non-motor symptoms**	MDS-NMS scale, Scopa-Aut

**Table 2 pone.0293774.t002:** Phase 2 in Portugal. Assessment of surrogate patterns for mitochondrial (dys)function in patients’ fibroblasts using molecular biology techniques.

Primary outcome measures	Specific objectives	Description	Mitochondrial function analysis
Evaluate the effect of PA on mitochondrial remodeling in skin fibroblasts from patients with PD, namely in the mitochondrial maximal respiration	Assess the effects of metabolic remodeling on mitochondrial oxygen consumption rate, oxidative stress, mitochondrial quality control, mitochondrial DNA copy number, mitochondrial proteins and transcripts	Characterize the effects of PA remodeling on fibroblast from patients with PD, in terms of mitochondrial biogenesis, oxidative stress, and mitochondrial quality control	- Determination of oxygen consumption rate (OCR) and extracellular acidification rate (ECAR) using a Seahorse XFe96 Extracellular Flux Analyzer (Agilent Technologies, Germany). - qRT-PCR (using SsoFast Eva Green Supermix, in a CFX96 real time-PCR system (Bio-Rad, Hercules, CA, USA)) for transcripts of interest related to mitochondrial biogenesis, dynamics, epigenetic regulation, oxidative phosphorylation, oxidative stress (SOD1, SOD2, NFE2L2), quality control mechanisms, including autophagy and ubiquitin-proteasome system (UPS). - Regulation and abundance of mitochondrial proteins by immunoblotting Enzymatic activities (ex, mitochondrial complex I and citrate synthase)

### Baseline assessment

Each participant will need to sign an informed consent prior to being interviewed. The interview will include a comprehensive medical history review and a complete anamnesis including the collection of medication control, gathering data on their current health status and also the chronology of their specific pathology. The clinical history and neurological examination will be prepared to confirm inclusion-exclusion criteria, assessing motor strength, muscular tone and pathological reflexes. Familiarization sessions will also be conducted before the intervention. In this session, the participants will be provided with a smart band (Amazfit Band®) in order to normalize the basal levels of PA that the patients may have throughout the study.

Both intervention and control groups will undergo a baseline evaluation, including
functional
assessment, PA
tests, motor
assessment, medication control, health
assessment and skin biopsy (small tissue samples) for fibroblast extraction from the skin of the neck.

### Baseline evaluation

A battery of tests will be performed (Figs 1 and 2), encompassing a complete neurological examination to confirm inclusion-exclusion criteria using the MDS-UPDRS questionnaire; psychological tests aimed at assessing cognitive aspects include the MoCA questionnaire; quality of life (using the PDQ39 questionnaire), mood (using the BDI-2 questionnaire), balance (TINETTI), sleep (PDSS test), and dysautonomia (SCOPA-AUT test). The 6-minute walk test (6MWT) to evaluate the functional capacity and endurance of participants will be conducted according to standardized guidelines. These tests and questionnaires will be evaluated pre- and post-intervention (at 3 months) and 3 months after the end of the intervention (6 months after the initial evaluation).

The complexity and extent of motor and non-motor symptoms of PD inevitably lead to a complex pathway of multidrug medication use, generally referring to the use of 5 or more medications at the same time [32,33]. In the same line, a meta-analysis showed that there is a high risk of polypharmacy and hyperpolypharmacy in older patients with PD [34]. Furthermore, extended use of levodopa may result in motor fluctuations and involuntary movements known as levodopa-induced dyskinesia (LID) [35]. Nevertheless, exercise can enhance the effectiveness of levodopa, leading to improved motor response, while also preventing biochemical changes (primary plasticity) in specific basal ganglia regions implicated in the development of LID [36]. To this end, we will obtain the complete medication history from each participant, including details of all prescribed medications, over-the-counter drugs, and supplements. Name, dosage, frequency, and duration of each medication will be documented. Prior to the intervention, participants would be instructed to continue their regular medication regimen without making any changes unless advised by their healthcare provider. Throughout the study, participants would be regularly reminded to report any changes or adjustments.

### Health assessment

A comprehensive health
assessment
will be conducted by
the Neurodegenerative Diseases Research Group at VHIR to compile a complete
medical
history. Health parameters (heart rate, blood pressure, anthropometric measurements, height, weight, BMI) will be determined before and after intervention.

